### Sham Acupuncture Group

Participants in the SA group will receive minimal acupuncture at sham acupoints, which are located at a horizontal distance of one B-cun (≈ 20 mm) to the points used in the acupuncture group.

For sham EX-B3, BL18, BL20, and BL21, needles will be vertically inserted at a depth of 1–2 mm without any manipulation to avoid de-qi sensation and will be withdrawn immediately afterward.

For sham GV20, GV29, LI11, CV12, CV10, ST25, CV6, CV4, ST40, and SP6, needles will be vertically inserted at a depth of 1–2 mm without any manipulation to avoid the de-qi sensation. The needles will be retained for 30 min during each treatment session.

### Lifestyle Recommendation

Lifestyle recommendations will be made based on expert consensus and previous large-scale studies (45, 46). After randomization, participants in both the acupuncture and the SA groups will receive a brochure with lifestyle recommendations and a 20–30-min face-to-face communication with related specialists on the importance of a healthy lifestyle for the management of IGT and obesity. Specifically, the participants will be encouraged to lose 5∼10% of their initial weight *via* an integrated strategy of diet and exercise. They will be encouraged to limit calorie intake, reducing at least 400–500 kCal daily, to increase their activity gradually according to their individual situation, with the goal of over 30-min medium-or high-intensity physical activities such as brisk walking. Medium- or high-intensity physical activities are defined as reaching 50-70% of the maximum heart rate, being a little strenuous, and having fast breathing but no shortness of breath during exercise. The participants will be encouraged to avoid excessive alcohol intake and quit smoking. Whether these recommendations have been accepted and conducted will be evaluated during each visit.

### Rescue Medication

The participants will not be encouraged to receive any other treatment or medication for IGT or obesity/overweight during the study period to avoid any influence on the results. If participants receive any other treatment, they will also be included in this study, but all details will be recorded in the case report form.

If diabetes is diagnosed during the study period and regular hypoglycemic drugs are recommended by the specialists, the participants will be allowed to use hypoglycemic drugs for rescue. The details (name, dosage, frequency, start time, and duration of use) of drugs will be documented. The proportion of participants using rescue drugs in the groups will be compared.

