### Outcome Measures

#### The Primary Outcome

The primary outcome will be change in the baseline value of 2hPG at the end of the 12-week treatment; 2hPG is the value of intravenous plasma glucose measured by 75 g OGTT, which is usually conducted to diagnose IGT and observe glucose metabolism (40). When the value of 2hPG fluctuates between 7.8 and 11.1 mmol/L, it will be regarded as IGT, and between 4.4 and 7.7 is the ideal control (40).

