#### Secondary Outcomes

(1) Change from baseline value of 2-h blood glucose on weeks 24 and 36.

(2) Proportion of participants whose 2-h blood glucose dropped to normal from baseline on weeks 12, 24, and 36.

(3) Proportion of participants with at least 5% reductions (47) in body weight from baseline on weeks 4, 8, 12, 16, 24, and 36.

(4) Change from baseline of body mass index (BMI) and waist-to-hip ratio (WHR) on weeks 4, 8, 12, 16, 24, and 36.

(5) Change from baseline of fasting plasma glucose (FPG), fasting serum insulin (FINS), homeostasis model assessment-insulin resistance index (HOMA-IR), TC (serum total cholesterol), TG (triglyceride), LDL-C (low-density lipoprotein cholesterol), and high-density lipoprotein cholesterol (HDL-C) on weeks 12, 24, and 36.

(6) Change from baseline of blood pressure on weeks 12, 24, and 36.

(7) Change from baseline in the Impact of Weight on Quality of Life-Lite Questionnaire (IWQOL-Lite) scores on weeks 4, 8, 12, 16, 24, and 36.

IWQOL-Lite is an international scale used to measure an individual’s health-related quality of life (48). A total of 31 questions are divided into five subscales: 11 questions concerning physical function, 7 concerning self-esteem, 4 concerning sex life, 5 concerning public pressure, and 4 concerning work. The score of each question is divided into five grades, with 5 representing always, 4 often, 3 sometimes, 2 rarely, and 1 never. The total score of the questionnaire is 155, with higher score indicating worse quality of life. The MCID of IWQOL-Lite is 12 (49) for overweight/obesity.

(8) Change from baseline in the Simplified Nutritional Appetite Questionnaire (SNAQ) scores on weeks 4, 8, 12, 16, 24, and 36.

The SNAQ scale is a short and simple appetite assessment tool that can predict weight loss in adults (50). It measures the amount of food per meal, the number of meals per day, and the taste of the food. It consists of four items, each with five grades and with the total score ranging from 4 to 20 points. Lower scores indicate deterioration in appetite (50).

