### Statistical Analysis

We will use the SPSS V.25 software (IBM Corp., Armonk, NY, United States) to perform all statistical analyses following the intention-to-treat principle. CI will be established at 95% and significance level at 0.05. Missing data will be calculated using the actual observational value without imputation if the dropout rate is no more than 5%. For continuous data, the data will be presented as mean ± *SD* if normally distributed or as median (IQR) if not normally distributed. Longitudinal continuous data will be compared between the groups by repeated-measures analysis of variance (ANOVA) including group and time–group interaction. Other continuous data will be analyzed by Student’s *t*-test and Wilcoxon rank-sum test, and categorical data by X ^2^ test or Fisher’s exact test, as appropriate. Linear correlation analysis will be conducted to measure the closeness of linear correlation between variables. Sensitivity analysis will be performed if necessary. A *p*-value < 0.05 will be considered statistically significant.

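### Secondary outcome 2 counts a participant who became diabetic and was brought to normal glucose by rescue drugs as a success; outcome 3 has the same gap after other weight-loss treatment

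*Protocol article*

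**What the plan says.** All references are to the protocol article.

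- **Rescue Medication, trigger and permission.** "If diabetes is diagnosed during the study period and regular hypoglycemic drugs are recommended by the specialists", then "the participants will be allowed to use hypoglycemic drugs for rescue". Drug name, dosage, frequency, start time and duration are documented.
- **Rescue Medication, other treatment.** Other treatment for IGT or weight is discouraged because it could influence the results. However, "If participants receive any other treatment, they will also be included in this study", with details recorded in the case report form.
- **Rescue Medication, analysis.** One analytic use of the rescue data is stated: "The proportion of participants using rescue drugs in the groups will be compared".
- **Secondary Outcomes, item 2.** "Proportion of participants whose 2-h blood glucose dropped to normal from baseline on weeks 12, 24, and 36". No drug-free condition is attached.
- **Secondary Outcomes, item 3.** The proportion losing at least 5% of body weight at weeks 4, 8, 12, 16, 24 and 36, with no condition on other weight-loss treatment.
- **Statistical Analysis.** SPSS will be used "to perform all statistical analyses following the intention-to-treat principle". The missing-data rule concerns dropout only, and sensitivity analysis is left to need.

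**The concern.** Progression from IGT to diabetes is the outcome the intervention is meant to prevent. A participant who progresses has failed on the assigned treatment. If a glucose-lowering drug then brings the 2-h value into the normal range, item 2 records the same person as one whose glucose returned to normal.

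A responder rate built this way mixes two opposite courses: recovery on acupuncture or sham, and progression followed by drug treatment. The stated aim is to compare acupuncture with sham acupuncture for improving glucose metabolism, and the Discussion stresses returning glucose to normal during the IGT stage. A reader would take the item 2 proportion as evidence on that question. At stake are the level of the responder rate in each arm and, if drug use differs between arms, the contrast between them.

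**Working it through.** **Does the misclassification follow from the text?** Take a participant with a baseline 2hPG in the IGT range (7.8 to 11.1 mmol/L).

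1. The week-12 OGTT shows diabetes, the specialists recommend a drug, and it is started, as Rescue Medication permits.
2. The week-24 2hPG is below 7.8 mmol/L under the drug.
3. The participant stays in the analysis. Intention-to-treat applies to all analyses, and nothing excludes or reclassifies rescued participants.
4. Item 2 asks only whether 2hPG has dropped to normal from baseline. It has, so the participant is a success at week 24.

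The same steps apply to item 3 for someone who starts another weight-loss treatment and then passes 5%. The exclusion criteria bar antidiabetic and weight-loss treatment in the 3 months before entry, so nearly all such treatment would be a new start on study, which a start date can identify.

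**How many participants?** Inputs:

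- Progression without intervention: about 7% per year (Introduction).
- 98 participants per arm (Sample Size Calculation).
- 2hPG after baseline at weeks 12, 24 and 36 only (Secondary Outcomes; the islet-function row of Table 1 has the same visits).
- Assumptions: every diagnosed case is rescued and every rescued case is normalised. Both push the count up.

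Cumulative progression by week w is 1 − (1 − 0.07)^(w/52):

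- Week 12: 1 − 0.93^(12/52) = 0.0166, × 98 = 1.6
- Week 24: 1 − 0.93^(24/52) = 0.0329, × 98 = 3.2
- Week 36: 1 − 0.93^(36/52) = 0.0490, × 98 = 4.8

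A case found at one scheduled test can be drug-treated only before the next. So the week-12 count bears on week 24, and the week-24 count on week 36. The Introduction's 7% is for no intervention, but both arms receive lifestyle recommendations. The Introduction also reports that lifestyle modification cuts the risk by more than half, though with poor adherence. Halving the rate to 3.5% gives 1 − 0.965^(12/52) = 0.0082 and 1 − 0.965^(24/52) = 0.0163.

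| Visit | Ceiling per arm, 7%/year | At 3.5%/year |
|---|---|---|
| Week 12 | about 0 | about 0 |
| Week 24 | 1.7% (1.6 of 98) | 0.8% (0.8 of 98) |
| Week 36 | 3.3% (3.2 of 98) | 1.6% (1.6 of 98) |

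If diagnoses could also be made and treated at any time between tests, the outer limits at 7% per year are 1.7%, 3.3% and 4.9% at weeks 12, 24 and 36.

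**What does this do to the comparison?** Each misclassified participant adds 1/98 = 1.0 percentage point to the arm's responder rate. The contrast shifts by the difference in misclassified proportions. Illustration at week 36, assuming 3.3% in sham and half of that (1.65%) in acupuncture: the difference shrinks by 3.3 − 1.65 = 1.65 points. If the two arms swap, it is exaggerated by the same amount. With equal proportions it does not move, but both rates are too high.

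For item 3 the documents give no rate of other weight-loss treatment, so no size can be put on it.

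**The case against.** **It is an omission that the statistical analysis plan may fill.** The article is condensed, and handling of values after rescue is often left to that plan, which is not shown and may contain a rule. This has weight for the continuous outcomes. It has less for item 2, because the article itself states the endpoint, the rescue pathway and the analysis principle, and together these already give a classification.

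**What is stated is coherent.** Keeping treated participants, analysing by intention-to-treat and comparing rescue use between arms is a recognised treatment-policy approach. This stands for mean 2hPG. A reader might infer that every glucose value measured under rescue is wrongly analysed. The documents do not support that: such an analysis estimates the effect regardless of rescue, which is a legitimate question.

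**The primary outcome is hardly touched.** "The primary outcome will be change in the baseline value of 2hPG at the end of the 12-week treatment". Diabetes found at the week-12 test is treated after that value is taken. A reader might infer a material loss of power for the primary comparison, but that needs rates of drug use before week 12 that the documents do not give.

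**The effect on later means is easily overstated.** A reader might apply the whole 36-week progression to both follow-up visits. With 5% rescued in sham, 2.5% in acupuncture and an assumed drug effect of 2 to 4 mmol/L, the shift is 0.025 × 2 to 4 = 0.05 to 0.10 mmol/L, or 26 to 53% of a difference of 0.19. With the timing above and the same 2:1 split, it is 0.0083 × 2 to 4 = 0.017 to 0.033 at week 24 (9 to 17%) and 0.0165 × 2 to 4 = 0.033 to 0.066 at week 36 (17 to 35%). Even these need an assumed imbalance and drug effect. The 0.19 also assumes that a minus sign was lost before 0.97 in the sample-size section (1.16 − 0.97); as printed, the difference is 2.13. It is moreover a planning figure for the primary outcome, not for weeks 24 and 36.

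**The direction is not fixed.** More rescue in sham is plausible if acupuncture works, but the documents do not establish it.

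**Conclusion.** The point holds for the responder outcomes. As written, item 2 scores drug-induced normalisation after progression to diabetes as success, and item 3 has the same flaw after other weight-loss treatment.

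The size is small: at most about 1.7% of an arm at week 24 and 3.3% at week 36, almost none at week 12, and about half of that if lifestyle advice halves progression. These ceilings rest on the article's 7% yearly rate, detection at scheduled tests only, and rescue and normalisation of every case. Diagnoses between tests, or glucose-lowering treatment taken outside the rescue rule, would add to them. Bias in the contrast is toward no difference if sham uses more drugs and the reverse if acupuncture does.

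The documents do not support extending this to the primary outcome or calling the all-data analysis of mean 2hPG an error. The correction is worth making because a failure is labelled a success and the remedy is cheap, not because the trial's main conclusion is at risk.

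**What to change.** Leave the clinical rescue rule unchanged and amend only the analysis, before unblinding:

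1. **Item 2.** Count a participant as not normalised at every visit after the recorded start of a glucose-lowering drug.
2. **Item 3.** Count a participant as not having reached 5% at every visit after the recorded start of other weight-loss treatment.
3. **Mean 2hPG.** Keep the analysis of all observed values and state that it estimates the effect regardless of rescue or other treatment.

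I would not add an analysis that replaces values after rescue with values imputed from un-rescued participants. It would assume that people who progressed to diabetes would have behaved like those who did not, and so would flatter the arm with more failures.

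The cost is a few sentences and a slightly lower stated responder rate. The start time of rescue drugs is already documented. For other treatment the case report form is to hold all details, so check only that the start date is among them.

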### Outcome Measures

#### The Primary Outcome

The primary outcome will be change in the baseline value of 2hPG at the end of the 12-week treatment; 2hPG is the value of intravenous plasma glucose measured by 75 g OGTT, which is usually conducted to diagnose IGT and observe glucose metabolism (40). When the value of 2hPG fluctuates between 7.8 and 11.1 mmol/L, it will be regarded as IGT, and between 4.4 and 7.7 is the ideal control (40).

#### Secondary Outcomes

(1) Change from baseline value of 2-h blood glucose on weeks 24 and 36.

(2) Proportion of participants whose 2-h blood glucose dropped to normal from baseline on weeks 12, 24, and 36.

(3) Proportion of participants with at least 5% reductions (47) in body weight from baseline on weeks 4, 8, 12, 16, 24, and 36.

(4) Change from baseline of body mass index (BMI) and waist-to-hip ratio (WHR) on weeks 4, 8, 12, 16, 24, and 36.

(5) Change from baseline of fasting plasma glucose (FPG), fasting serum insulin (FINS), homeostasis model assessment-insulin resistance index (HOMA-IR), TC (serum total cholesterol), TG (triglyceride), LDL-C (low-density lipoprotein cholesterol), and high-density lipoprotein cholesterol (HDL-C) on weeks 12, 24, and 36.

(6) Change from baseline of blood pressure on weeks 12, 24, and 36.

(7) Change from baseline in the Impact of Weight on Quality of Life-Lite Questionnaire (IWQOL-Lite) scores on weeks 4, 8, 12, 16, 24, and 36.

IWQOL-Lite is an international scale used to measure an individual’s health-related quality of life (48). A total of 31 questions are divided into five subscales: 11 questions concerning physical function, 7 concerning self-esteem, 4 concerning sex life, 5 concerning public pressure, and 4 concerning work. The score of each question is divided into five grades, with 5 representing always, 4 often, 3 sometimes, 2 rarely, and 1 never. The total score of the questionnaire is 155, with higher score indicating worse quality of life. The MCID of IWQOL-Lite is 12 (49) for overweight/obesity.

(8) Change from baseline in the Simplified Nutritional Appetite Questionnaire (SNAQ) scores on weeks 4, 8, 12, 16, 24, and 36.

The SNAQ scale is a short and simple appetite assessment tool that can predict weight loss in adults (50). It measures the amount of food per meal, the number of meals per day, and the taste of the food. It consists of four items, each with five grades and with the total score ranging from 4 to 20 points. Lower scores indicate deterioration in appetite (50).

### Expectation Assessment

Participants’ expectations of acupuncture will be evaluated with reference to previous high-quality acupuncture clinical trials (51, 52). The participants will be assessed at baseline by the following two questions: “Do you think acupuncture will be effective in treating the illness?” and “Do you think acupuncture will be effective in controlling weight and decreasing glucose?” The response options will be “Ineffective,” “the effect is not good,” “uncertain,” “has some effect,” or “very effective.”

### Blinding Assessment

Blinding will be assessed using the James and Bang blinding indices (53). The participants will be told that they are 50% likely to be allocated to the traditional acupuncture group with deeper needling or to the modern acupuncture group with shallower needling. After the last treatment on week 12, each participant will be assessed with a questionnaire asking, “do you receive traditional acupuncture?,” with choice options of Yes or No.

### Compliance Assessment

(1)Compliance assessment of acupuncture

Compliance on acupuncture will be estimated by counting how many times the subjects have received the treatment, and the criterion for good compliance will be 80% and above. The calculation formula is as follows: compliance = (the number of times the subject has received treatment/the total number of times the subject should receive the treatment) × 100%.

(2)Compliance assessment of life recommendation

The participants lifestyle adjustment diary card, dietary change table, dietary compliance questionnaire, and exercise compliance scale were selected to evaluate the compliance on lifestyle recommendation.

The participant’s lifestyle adjustment diary card is a record of the completion of daily life guidance (complete “√,” unfinished “ × ,” to be checked every day). The dietary compliance questionnaire is extracted from the dietary treatment compliance questionnaire for patients with type 2 diabetes mellitus (54). It contains four questions concerning whether they eat strictly according to the dietary instruction plan, regular and quantitative meals, weigh or accurately measure food per meal, and use the Food Exchange scale to arrange their diet. Each question is provided with four options: it cannot be done at all, it can be done occasionally, it can be done basically, and it can be done completely.

The dietary change table before and after treatment included staple food and high-calorie non-staple food, and the options included “more than before treatment,” “more increase than before treatment,” “no change,” “less than before treatment,” and “more reduction than before treatment.”

The exercise compliance scale refers to the exercise compliance section of the coronary heart disease self-management scale (55). The question is “how did you participate in the recommended activities and exercise in the past month?” The options are: never participated in recommended activities (such as brisk walking, swimming, dancing, and Taijiquan), participated in recommended activities for less than 30 min per week, participated in recommended activities for 30–60 min per week, participated in recommended activities for 1–3 h a week, or participated in recommended activities for more than 3 h a week.

The specific outcome measures and time frame are displayed in Table 1.

**TABLE 1 T1:** Study schedule.

Period	Run-in period	Treatment period			Follow-up period		
Day	7–0 days	4 weeks	8 weeks	12 weeks	16 weeks	24 weeks	36 weeks
Informed consent	√						
Inclusion/exclusion criteria	√						
Demography characteristics	√						
Medical history	√						
Anthropometry	√	√	√	√	√	√	√
Islet function	√			√		√	√
Blood lipid	√			√		√	√
Blood pressure	√			√		√	√
SNAQ	√	√	√	√	√	√	√
IWQOL-Lite	√	√	√	√	√	√	√
Expectation assessment	√						
Blindness assessment				√			
Combined use of drugs	√	√	√	√	√	√	√
Adverse events	√	√	√	√	√	√	√
Compliance assessment of acupuncture				√			
Compliance assessment of Lifestyle recommendation		√	√	√	√	√	√

*IWQOL-Lite, Impact of Weight on Quality of Life-Lite Questionnaire; SNAQ, Simplified Nutritional Appetite Questionnaire.*

### Safety Assessment

Adverse events (AEs) will be reported by the participants themselves and evaluated by outcome assessors and recorded in detail on AE forms throughout the study period. Based on their potential association with the intervention, AEs will be categorized by acupuncturists and related specialists as treatment-related or non-treatment-related within 24 h of occurrence. Treatment-related AEs include but not limited to broken needles, hematoma, infection, abscess around the location of the needle insertion, fainting, vomiting, nausea, palpitations, dizziness, anorexia, and insomnia that presented during or after acupuncture. Non-treatment-related AEs refer to any other unexpected AE that happened after the initiation of the study. According to the evaluation criteria of the NHS Committee (56), AEs will be divided into three levels (severe, moderate, and mild). Standardized procedures for AE management, especially for serious AEs, will be prepared, and all researchers and doctors involved will be trained.

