As an important Traditional, Complementary, and Integrative Medicine (TCIM) therapy, acupuncture treatment has been more and more adopted in clinical practice all over the world. Its efficacy and safety have been preliminarily demonstrated in the treatment of insulin resistance (IR)-related diseases such as obesity, diabetes and its related complications, polycystic ovary syndrome, and hypertension (31–36). Although the physiological and pathological mechanisms of IGT are also related to IR (37, 38), the potential role of acupuncture in the treatment of obese people with IGT has not yet been determined by a well-designed randomized controlled trial (RCT). Therefore, this study is conducted to evaluate the efficacy and safety of acupuncture versus sham acupuncture (SA) on improving glucose metabolism among IGT people with Overweight/Obesity.

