### Blinding

The participants will be blinded to the group allocation in this study, while the acupuncturists will not be blinded. The outcome will be evaluated by independent assessors who will be blinded to the allocation to minimize the bias associated with data collection. The statisticians will also be blinded to the allocation.

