### Intervention

Study group: acupuncture + lifestyle recommendation; control group: sham acupuncture + lifestyle recommendation.

During the 12-week treatment, participants in both the acupuncture and SA groups will receive 30-session treatment, three times per week (once every other day) in the first six weeks and twice per week (with an interval of 2–3 days) in the last six weeks. Certified acupuncturists with no less than one year of clinical experience will perform the treatment. Acupuncture needles (Huatuo, Suzhou Medical Appliance) with the size of 0.3 mm × 40-75 mm will be used in the acupuncture group, while, acupuncture needles (Huatuo, Suzhou Medical Appliance) with the size of 0.2 mm × 25-40 mm will be used in the SA group. The participants in different groups will be treated separately to avoid contamination during the process.

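### Unblinded acupuncturists share in deciding whether an adverse event is treatment-related, so the related/unrelated split, though not the all-AE count, could reflect knowledge of the arm

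*Protocol article*

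**What the plan says.** Three sections of the protocol article bear on this point.

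- **Safety Assessment.** Ascertainment comes first: "Adverse events (AEs) will be reported by the participants themselves and evaluated by outcome assessors and recorded in detail on AE forms". Attribution is then given to other people: "AEs will be categorized by acupuncturists and related specialists as treatment-related or non-treatment-related within 24 h of occurrence". The section guides that call with a list: "Treatment-related AEs include but not limited to broken needles, hematoma, infection, abscess around the location of the needle insertion, fainting, vomiting, nausea". The list goes on to palpitations, dizziness, anorexia and insomnia arising during or after a session. Any other unexpected event counts as non-related.
- **Blinding.** "The participants will be blinded to the group allocation in this study, while the acupuncturists will not be blinded". Of the assessors it says: "The outcome will be evaluated by independent assessors who will be blinded to the allocation to minimize the bias associated with data collection". Statisticians are also blinded.
- **Intervention.** "Certified acupuncturists with no less than one year of clinical experience will perform the treatment".

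The Introduction makes safety against sham acupuncture a stated aim, next to efficacy. The Discussion lists the unblinded acupuncturist as a possible source of bias in general terms and does not mention adverse-event attribution.

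**The concern.** Acupuncturists are the one role the article describes as unblinded. They also perform the procedure and take part in judging whether it caused harm. They know whether they needled deeply with manipulation or only 1–2 mm without it, and that knowledge could influence the call on an ambiguous event in either arm. It could also work in either direction: a shallow needle may seem an unlikely cause, and a practitioner may be slow to attribute harm to their own deep needling.

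What is at stake is how the treatment-related adverse-event rates by arm are read. Readers will take them as coming from a trial with blinded assessment, although this classification was not made blind.

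**Working it through.** The article gives no figure for this point, so the check is a comparison of its statements.

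1. **Who makes the call.** Safety Assessment names two parties, acupuncturists and related specialists. Blinding says the first are unblinded, and Intervention says they treat. For the second, no blinding status is given, nor is there a rule for disagreement. At least one party to the decision therefore always knows the arm.

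2. **What that party can see.** In the acupuncture arm the stated depths are 15–25 mm at the back points and 25–35 mm at the trunk and limb points, with manipulation to obtain *de qi*. In the sham arm the depth is 1–2 mm without manipulation. The treating acupuncturist cannot miss the difference.

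3. **How much judgement is left.** Listed symptoms count as related if they arise during or after acupuncture, with no distinction by arm. That is a type-and-timing rule and it narrows discretion. Three features leave room: classification rests on potential association with the intervention, the list is explicitly not exhaustive, and the period after acupuncture has no end. Insomnia some days after a session, or a symptom not on the list, still needs a decision.

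4. **What lies upstream.** Participants, who are blinded, report the events. Outcome assessors evaluate and record them. Taking these to be the independent assessors of the Blinding section, they are blinded too. Whether an event is counted at all therefore does not depend on the acupuncturists; only its label does.

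5. **Size.** This cannot be computed, because the article gives no adverse-event rate and no attribution rate. The following is an illustration on assumed values only. Let n = 98 per arm (the planned number), let the true proportion with an event be a in both arms, and let fractions s1 and s2 of these be labelled related. Then p1 = a·s1, p2 = a·s2, p̄ is their mean, and the chance of a spurious difference at two-sided 0.05 is approximately

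   Φ{ [ |p1 − p2| − 1.96·√(2p̄(1 − p̄)/n) ] / √[ (p1(1 − p1) + p2(1 − p2))/n ] }.

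   For a = 20%, s1 = 40% and s2 = 60%: p1 = 0.08, p2 = 0.12, p̄ = 0.10. The first root is √(0.18/98) = 0.0429, and 1.96 times it is 0.0840. The second root is √(0.1792/98) = 0.0428. The argument is (0.04 − 0.0840)/0.0428 = −1.03, so the chance is about 15%, against a nominal 5%.

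| Assumed event rate, both arms | 40% v 60% labelled related | 30% v 70% labelled related |
|---|---|---|
| 10% | about 9% | about 25% |
| 20% | about 15% | about 46% |
| 30% | about 22% | about 65% |

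The table shows how unequal labelling would act if it occurred. It is no evidence that it will occur, and the rule in step 3 makes the wider splits less plausible.

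**The case against.** The case for leaving the text alone has real substance. The acupuncturists do not decide alone. The listed symptoms are assigned by type and timing in both arms alike, so calling nausea unrelated because the needle was shallow would depart from the section's own rule. Events are collected and evaluated by blinded people before any attribution. Monitors check the adverse-event tables weekly, and AE procedures and training are promised. The treating practitioner has first-hand knowledge of a broken needle, a haematoma or a faint. The article names no between-arm test of related events, and the choice of safety tables normally belongs to an analysis plan, which is not at hand.

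Most of this limits the point without removing it. A shared decision is still partly unblinded, and the specialists' blinding is not stated. The list narrows discretion but does not close it. Weekly monitoring does not change who classifies. First-hand knowledge is a reason for acupuncturists to report the facts; it does not require them to assign the label. The limitation in the Discussion is put down to the nature of acupuncture. That explains unblinded delivery, but attribution could be blinded. Nor is this a detail lost in condensing: the article states who classifies.

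A reader might infer that acupuncturists alone settle causality, or that the whole safety comparison is compromised. The text supports neither: specialists share the call, and the all-AE count rests on blinded reporting and evaluation.

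**Conclusion.** The point holds for the split into treatment-related and non-related adverse events. A role that is unblinded and delivers the treatment takes part in a classification that retains some judgement, and the plan states no blinded check on it. The comparison of all adverse events is much less exposed. The primary outcome is a laboratory glucose value, and efficacy inference is unaffected.

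Neither size nor direction can be derived from the document. A reader might take the illustrative error rates above as an estimate, or infer a predictable tilt against one arm. Neither is supported, since the attribution fractions and event rates are assumed and the influence could run either way.

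The conclusion assumes that the outcome assessors who evaluate adverse events are the blinded assessors of the Blinding section, and that no blinding of the specialists is laid down elsewhere. If the full protocol keeps the specialists blinded and gives them the final word, little of the point remains. It is a modest, avoidable weakness in a stated safety aim.

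**What to change.** Amend Safety Assessment so that relatedness is assigned from the AE form by the blinded outcome assessors who already evaluate each event, or by specialists who are stated to be kept blinded to allocation. Limit the acupuncturists to supplying the facts of the event, recorded without naming the arm. Report all adverse events by arm regardless of attribution, alongside the table of related events.

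The cost is a change of wording and some care over what the form discloses. With the outcome assessors in this role, no new staff are needed. Sample size, visits and treatment are untouched. The downside is that needle-site events may reveal the arm to the person classifying them, so their attribution should be reported descriptively and not presented as a blinded judgement.
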